#### Intervention Fidelity and Data Collection

2.4.3

Guided by the well-regarded RE-AIM framework [123], our proposed mixed-method study design will explore the Reach, Efficacy, Adoption, Implementation, and Maintenance of the LEAD clinical trial. The RE-AIM framework will guide the development and evaluation of this behavioral intervention. The LEAD clinical trial platform will integrate study design (i.e., consent and data collection) and intervention delivery into a unified system, allowing the investigators to continually and systematically manage and track enrollment, consent, intervention completion, and data capture using standard metrics.

The sample is fully powered to get parameter estimates for the feasibility, usability, acceptability, and initial efficacy of the LEAD clinical trial. The proposed mixed-method study will allow us to evaluate study hypotheses while exploring the proposed mechanism of action underlying the intervention’s effect. The LEAD Guide is the foundation of the LEAD clinical trial; it is a published and publicly accessible advance care planning tool that will promote reproducibility. We plan to share all data and resources following the University of Utah and NIH policies. Our data-sharing plan includes storing data in the National Alzheimer’s Coordinating Center, a National Institutes of Health-funded repository.

### Measures and Data Collection

2.5

#### Primary and Secondary Outcomes

2.5.1

Different data sources and measures will explore each of the three specific aims.

##### Aim 1:

To describe the acceptability, usability, and feasibility of the LEAD clinical trial, we will use data from the web-based feasibility surveys conducted immediately after the completion of Modules 1, 2, and 3, as well as analytics tracked in the back-end database of the intervention.

To assess feasibility, we will use measures including the time required to identify and recruit 60 dyads, the percent of the enrollment of eligible participants (60/100, or 60%), and retention rate and data completion (85% retention at the end of the intervention; 75% retention to 14-week follow-up; 70% through 20-week follow-up).

To assess the acceptability, feasibility, and appropriateness of the LEAD clinical trial, we will use a validated scale developed by Weiner et al. [130] (Cronbach’s α = 0.85 to 0.91). Each domain includes four Likert-type questions from 1 (Completely Disagree) to 5 (Completely Agree). Our benchmark for success will be a mean of the four items ≥ to 4 on each domain. We will ask a final open-ended question, “Do you have any comments or suggestions for the LEAD clinical trial?” for intervention refinement.

The usability of the LEAD clinical trial is related to end-user behaviors using Google Analytics to describe participant navigation and utilization of the LEAD clinical trial features. These data will describe, for example, which features and resources are utilized the most by participants. These data will also track which participants created, stored, or shared advance care planning documents within the functionality of Module 3.

##### Aim 2:

To assess the initial efficacy of the LEAD clinical trial on the primary (decision-making self-efficacy) and secondary outcomes (relationship quality, subjective well-being, anxiety) as perceived by both the care recipient and the care partner. Table 3 presents the quantitative measures for the primary and secondary outcomes.

##### Aim 3:

To examine advance care planning congruence as a mechanism of action for the LEAD clinical trial. During Module 1, members of the dyad will complete the Lead Guide individually. The care recipient completes the guide for him- or herself, and the care partner completes it as if they were the care recipient. The LEAD Guide questions examining congruence are composed of two types: end-of-life values and preferences using the care recipient’s preferences/values as the “gold standard.” The first category is questions related to end-of-life values on a Likert-type, 1 to 5 scale; for example, “I am concerned about being a financial burden to family or close friends,“ rated from Strongly Disagree to Strongly Agree. Congruence between dyads is the absolute difference between the care partner and the care recipient on a question (e.g., the care partner endorses strongly agree (score of 5) while the care recipient endorses agree (score of 4), leading to an absolute difference of one unit). Reverse scoring each difference will make it such that summing across all questions of interest, higher scores indicate higher congruence.

The second category is end-of-life preferences; for example, “I prefer that decisions related to the location of ongoing care be made by” the care recipient alone, the care recipient with family and doctor, family/or doctor without the care recipient’s input, or uncertain. These will be coded between individuals as either Agree or Disagree. Again, higher scores would be indicative of more congruence. Descriptive statistics will summarize congruence during baseline. In Module 2, the dyad will complete the LEAD Guide together and engage in further advance care planning discussion. Qualitative assessment of advance care planning congruence is a positively weighted change toward a shared understanding of the care recipient’s end-of-life values and preferences. We collect additional indicators via surveys (collected at post-intervention and 20-week follow-up).

Finally, the baseline assessment includes participant demographics. These include age, race, ethnicity, gender, education level, income, comorbid health conditions, and the dyad relationship type. Charlson Comorbidity Index (CCI) [131], collected on the baseline survey, measures comorbidities. The CCI contains 19 health conditions (e.g., diabetes, renal disease), each weighted according to their potential influence on mortality. Each item is assigned a score of 1, 2, 3, or 6 based on the risk of mortality associated with each condition (range = 0–33, with higher scores indicating a greater risk of mortality).

#### Analytic Plan

2.5.2

A strength of using a mixed-method approach for the LEAD clinical trial is that it will allow us to triangulate measures to generate a comprehensive understanding of the LEAD clinical trial processes and outcomes. For Aim 1, we will systematically track and descriptively report variations using the LEAD clinical trial. Feasibility will be operationalized based on time to enrollment, survey completion, and design-related retention rate. Furthermore, we will implement the three-domain validated Weiner Scale described above to assess each module’s acceptability, feasibility, and appropriateness. We will also use responses from questions on the self-report surveys, utilizing both Likert-type responses and narrative text boxes. We will assess variation in the dosing (completion of modules and how many times module(s) needed to be revisited prior to completion) of intervention delivery. Dose outcomes will be reported separately for each module as the proportion of dyads that completed an advance directive and disseminated advance care planning documents by the end of the study. Dropouts are non-completers under an intention-to-treat analysis.

We will focus on the analysis of data video-recorded through the use of the LEAD clinical trial (dyad conversation in Module 2). These data will be entered into MAXQDA^©^ software and evaluated using qualitative conversation analysis [132, 133]. Conversation analysis utilizes existing dialogue practices and underlying normative organizations of interactions within dyads and the analysis of patterns exhibited across collections of cases. Conversation analysis permits the identification and interpretation of both action and sequence of conversation elements (turn-taking, repair, action formation, ascription, and action sequencing). These elements illuminate the process of shared progress toward an outcome (completion of the LEAD Guide and other outcome measures) [134, 135] (See Table 3 for details).

For Aim 2, we will assess the initial efficacy of the primary (decision-making self-efficacy) and secondary (relationship quality, anxiety, subjective well-being) outcomes for the dyads enrolled in the study. Because individuals are distinguishable (care recipient and care partner) and nested in pairs, bivariate response models are utilized to model the dyad for changes in outcomes across the study. We will utilize time as a categorical variable to allow more flexibility in examining evolution in the primary and secondary outcomes across the five-time points of baseline, midpoint, post-intervention, and 14-week and 20-week follow-ups. This process allows for separate estimation of fixed effects of means for the care recipient and the care partner and allows random variation for the baseline intercepts. Finally, because repeated measures are correlated, and measures between individuals nested in pairs are likely to be correlated, the models will include a covariance matrix that allows for these associations. Our alternative hypothesis is that mean decision-making self-efficacy and secondary outcomes will improve in the care recipient and care partner over time. Additional exploratory covariates will include the dose (number of completed modules), relationship type (spousal/partner versus child-parent), and care recipient gender.

Qualitative descriptive analysis [41, 42] identifies and analyzes themes from open-ended narrative responses associated with these outcome measures. This method emphasizes a “data-near” approach, accepting the respondent’s statement as an accurate representation of their experience.

For Aim 3, qualitative analysis creates profiles of dyads under different categories of both practical and dyad outcomes: ADRD status (preclinical or early stage ADRD), relationship type (spouse/partner or adult child), and education level (of the care recipient). Conversation analysis coding and interpretation will incorporate and expand on themes identified earlier using qualitative descriptive analysis. Coding will also explicate and interpret individual and dyadic responses to the use of the LEAD clinical trial, specifically the process of change in advance care planning congruence. The analysis will further illuminate the relationship quality of dyads and the decision-making self-efficacy of the care partner, providing innovative triangulation of data obtained from self-reported measures and providing a deeper and richer analysis for this aim.

Conversation analysis, coupled with descriptive qualitative analysis (of other narrative responses reported on surveys) and descriptive quantitative analysis (of scaled scores reported on surveys), will illuminate the change process in advance care planning congruence. Furthermore, analyses will illuminate change within the dyad as they move toward outcomes such as advance directive completion and dissemination of documents. We expect that some dyads will begin as highly congruent in their understanding of the care recipient’s goals of care in the context of dementia. Other dyads will proceed toward congruence as a function of the intervention. Still, others may remain incongruent despite the LEAD clinical trial. We will qualitatively explore these difficulties with respect to relationship quality, barriers within the LEAD clinical trial, and dyad type (preclinical vs. early-stage ADRD). Together, these results will provide insight into what types of dyads (e.g., poor relationship quality, higher level of cognitive impairment) might need facilitated support when using the LEAD clinical trial.

Quantitative analysis will explore the role of advance care planning congruence (scoring as described above) on decision self-efficacy in two ways: 1) Hypothesis testing that mean self-efficacy at baseline as well as collapsed over time will be positively associated with advance care planning congruence between the care partner and care recipient at baseline. 2) Describe how congruence at baseline predicts change in self-efficacy for both the care partner and care recipient. This sub-aim is interested in characterizing potential patterns of self-efficacy in dyads based on their initial congruence. We will graphically examine trajectories for patterns from our 60 dyads as well as estimate slopes of self-efficacy for potential interactions with congruence. For example, steep rates of improvement for dyads that start with low congruence and low self-efficacy that complete all modules compared with those with high congruence and baseline self-efficacy may have shallower slopes.

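### The sentence fixing per-module dose reporting uses advance-directive completion and document sharing, a Module 3 end-of-study outcome, and so conflicts with the plan's own definition of dose as module exposure

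*Protocol article*

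**What the plan says.** Section 2.5.2 (Analytic Plan) of the protocol article uses the idea of dose three times.

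- **Aim 1, definition.** The plan will assess variation in dosing, described as "completion of modules and how many times module(s) needed to be revisited prior to completion". This is exposure to the intervention.
- **Aim 1, reporting rule, in the next sentence.** "Dose outcomes will be reported separately for each module as the proportion of dyads that completed an advance directive". The same sentence adds sharing of planning documents to the criterion and sets study end as the time point. The sentence after that counts dropouts as non-completers under intention-to-treat.
- **Aim 2, covariate.** The exploratory covariates include "the dose (number of completed modules"). This again is exposure.

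Under Aim 3 the same section refers to "outcomes such as advance directive completion and dissemination of documents", so there the two behaviours in the reporting rule are classed as outcomes.

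The Aim 1 paragraph also opens with a general commitment: "we will systematically track and descriptively report variations using the LEAD clinical trial".

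**The concern.** The plan defines dose as how much of the intervention a dyad received, then reports it as something the dyad achieved by the end of the study. The achievement belongs to one module, yet the rule applies it to all three.

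This is a Stage 1 feasibility study of a three-module sequence, and section 2.4.2 says that each step opens only once the one before it is finished. Where dyads stall is therefore a main feasibility result, and a per-module dose table is the natural place to show it. A table built to this rule would show a downstream result under the label of dose. The word would also mean exposure in the Aim 2 models and outcome in the Aim 1 tables, which invites misreading of any dose-response finding.

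**Working it through.** The plan gives no figure to reproduce, because the point concerns how a descriptive measure is defined. The check compares the definitions and then asks what the rule yields.

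**Step 1: which module do the two behaviours belong to?**
- Section 2.3.3 and Table 1 place formal documents and their sharing in Module 3.
- Section 2.5.1 (Aim 1) tracks the creation, storage and sharing of documents within Module 3, under usability.
- Module 1 is individual completion of the LEAD Guide. Module 2 is the recorded conversation and joint completion. Neither produces or shares an advance directive.

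**Step 2: does the measure vary by module?**
Let S be the number of dyads that meet the criterion by study end. S is a single status per dyad and carries no module term. With dropouts counted as non-completers, the natural denominator is all 60 enrolled dyads:

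- Module 1: S/60
- Module 2: S/60
- Module 3: S/60

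On this reading the three figures are identical whatever S is.

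**Step 3: what would exposure reporting show instead?**
Let C1, C2 and C3 be the numbers of dyads completing each module. Exposure is C1/60, C2/60 and C3/60. Section 2.5.3 expects 42 dyads to complete all three modules. Because the steps unlock in order, C3 = 42 at that expectation, and C1 and C2 each lie between 42 and 60:

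- Module 3: 42/60 = 70%
- Modules 1 and 2: from 42/60 = 70% to 60/60 = 100%
- Dyads not completing all three: 60 − 42 = 18

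Those 18 might all stop in Module 1, all stop in Module 3, or be spread across the three. S/60 cannot tell these cases apart. Module completion proportions can.

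**Step 4: does another denominator rescue the rule?**
Suppose the figure is meant among the completers of each module: S/C1, S/C2, S/C3. Assume that every dyad counted in S completed Module 3, and hence all three modules. The numerator is then constant and only the denominator shrinks. With C3 = 42 and C1 at its maximum of 60, the Module 3 figure exceeds the Module 1 figure by a factor of at most 60/42 = 1.43. The figures now differ, but each is an outcome rate in an exposure group and still not a dose.

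**Step 5: one proportion or two?**
The rule joins directive completion and dissemination with a plain conjunction. It can be read as one joint proportion or as two listed ones. A joint proportion cannot exceed the smaller of its two components, so the choice affects the reported value.

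**The case against.** The strongest reply is that the surrounding text already covers exposure. The same paragraph promises to assess module completion and revisits and to report variation in use descriptively. Section 2.4.3 says the platform tracks intervention completion, section 2.3.3 describes a dashboard of completed tasks, and Aim 2 models the number of completed modules. This stands. A reader might infer that the trial never reports exposure, or reports none by module. The documents do not support that.

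A second reply is that the sentence speaks of dose outcomes rather than dose, and may mean outcomes broken down by module completed, or may have lost a phrase in condensing. This stands in part. That the same figure appears three times follows from the literal all-dyads reading and is not stated in the article. However, the breakdown by completers is not stated either, fits poorly with the dropout sentence that follows, and would still not report dose.

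A third reply is that denominators and table layout belong in a fuller document. That would answer a complaint about missing detail. Here a specific rule is stated, and it disagrees with the definition beside it.

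The complaint about the conjunction is weak on its own, since two separate proportions may well be intended. It is worth settling only because the sentence has to be rewritten anyway.

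**Conclusion.** The concern holds in a limited form. The one sentence that fixes how dose is reported for each module uses a Module 3 end-of-study outcome and conflicts with the exposure definition in both the preceding sentence and Aim 2. The finding that the figure does not vary by module rests on two assumptions: all 60 enrolled dyads form the denominator, and dropouts count as non-completers. The second is stated, and the first is the natural consequence of it. The range of 70% to 100% for Modules 1 and 2 rests on the plan's own expectation of 42 full completers and on sequential unlocking.

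Severity is low. Only the Aim 1 descriptive summary is affected. The primary outcome, the Aim 2 model, the power statement and the data to be collected do not change. The inference that module exposure goes unreported altogether goes too far, because the plan commits to assessing it.

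**What to change.** Replace the reporting sentence in section 2.5.2 with two:

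1. For each module, dose will be reported as the proportion of the 60 enrolled dyads that completed it, together with the number of revisits, with dropouts counted as non-completers.
2. Advance-directive completion and document dissemination will each be reported once, as two separate end-of-study outcomes over the 60 enrolled dyads, with dropouts counted as non-completers.

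Keep the word dose for module exposure throughout, as Aim 2 already does.

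The cost is two sentences. According to sections 2.3.3, 2.4.3 and 2.5.1, the platform already tracks task and intervention completion and the creation and sharing of documents, and the plan already intends to assess revisits. No new data collection, sample size change or change to the efficacy analysis is needed.

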#### Sample Size

2.5.3

The sample has ample statistical power for the proposed analyses. For example, Aim 1 evaluates feasibility, acceptability, and usability. With a total sample of 60 dyads, we expect reasonable descriptive parameter estimates and narrow 95% confidence intervals for all quantitatively assessed indicators. For example, 60% enrollment starting from a population of 100 dyads has an estimated 95% CI of [50.2%, 69.8%]. Similarly, if we anticipate that 85% of participants complete the surveys post-intervention, a sample size of 60 dyads at baseline has an estimate and 95% CI of 85% [76%, 94%].

Aim 2 examines the initial efficacy of the LEAD clinical trial on primary and secondary outcomes over time utilizing bivariate response models. Power and sensitivity analysis were computed in MPLUS and SAS using a bivariate model with time as a categorical variable and accounting for repeated measures and nesting of dyads. For this study, we will assume differences between 0.2 and 0.4 SD for the care recipient and care partner over time. With 42 dyads (the number of dyads expected to complete all three modules), this gives us greater than 91% power to detect these effects for dyads with complete data. Because our bivariate model analyses use intention-to-treat data from all participants regardless of missing time points, this provides a conservative power calculation for our expected sample size of 60 dyads.

Analyses for Aim 3 are composed of both qualitative and quantitative sub-aims. The proposed study is powered to address Specific Aims 1 and 2 with 60 participant dyads. Aim 3 is descriptive, focusing on mean differences in decision-making self-efficacy based on advance care planning congruence and exploring patterns of change over time based on baseline congruence.

### Discussion

2.6

Our study is innovative because it utilizes the psychometrically validated LEAD Guide, developed by our team, as a basis for the intervention [79]. We used our preliminary data to guide the concept, design, and implementation of dementia-focused advance care planning protocols with diverse local groups, national samples of healthy adults, adults in the preclinical or early stage of ADRD, and current and former care partners in community-based settings. The LEAD clinical trial is also innovative because it applies to early cognitive decline stages. In addition, the LEAD clinical trial likely has utility for healthy adults and those at risk of or concerned about ADRD but not yet experiencing any symptoms related to cognitive decline. Previous research has provided ample evidence that advance care planning, particularly within the context of ADRD, can reduce unnecessary and unwanted healthcare utilization (e.g., hospitalization, feeding tube) and reduce the stress associated with making surrogate medical decisions at the end of life [56, 136].

The LEAD Guide can be used in clinical settings by healthcare providers to help guide difficult conversations about current and future care associated with progressive neurodegenerative diseases such as ADRD. Given the challenge of engaging in end-of-life planning conversations, the LEAD Guide can help focus the conversation and ensure that the patient’s values and preferences are discussed and documented for future reference.

The LEAD clinical trial design encourages care recipients and care partners to revisit and revise advance care planning as cognitive impairment worsens, the caregiving context changes, or complicating medical conditions arise. Thus, because it explicitly guides dyads to consider whether and how care values and preferences differ under these different types of scenarios, the LEAD clinical trial could be used as a general, comprehensive advance care planning tool. Lastly, the LEAD clinical trial is innovative in implementing ADRD caregiver and advance care planning intervention best-practice recommendations. Furthermore, it is the first advance care planning intervention that is dementia-focused, web-based, self-administered, and intended for community-based settings.

